## Abstract

**Background:**

With an ageing population in most Western countries, people are living longer but often with one or more chronic physical health problems. Older people in physically poor health are at greater risk of developing clinical depression. Cognitive Behavioural Therapy (CBT) and Problem Solving Therapy (PST) have both been found to be efficacious in treating late-life depression, however patients with “multi-morbidity” (i.e. more than one chronic condition) are often excluded from these trials. The aim of this study is to compare the efficacy of CBT and PST in treating older adults who have one or more chronic physical health conditions and a diagnosable depressive disorder. This study will be the first to explicitly target the treatment of depression in older people in primary care settings presenting with a range of health problems using behavioural interventions.

**Methods/design:**

The PROMISE-D study is a randomised controlled trial of two evidence-based treatments for late-life major or minor depression for patients who also have at least one co-morbid chronic health problem. Participants will be randomised to two active interventions (PST or CBT) or enhanced treatment-as-usual (E-TAU). Primary outcomes will be depression diagnostic status and severity of depression (according to the Hamilton Depression Rating Scale and the Geriatric Depression Scale). Secondary outcomes will be anxiety severity, quality of life and health care utilisation. Assessments will be conducted by a researcher who remains blind to the patient’s treatment allocation and will be conducted pre and post-treatment and at six and 12 months follow-up. Health care utilisation will be assessed throughout a two year period following entry to the trial. Executive function, rumination and emotion regulation will also be measured to determine the impact of these factors on treatment response in two treatment groups.

**Discussion:**

Multi-morbidity, the experience of two or more chronic health problems, is becoming an increasing problem internationally, particularly amongst the elderly. Evidence-based psychological treatments exist for late-life depression and these have been shown to be effective for participants with individual health problems and depression. However, there are no studies that have compared the two leading psychotherapies shown to be effective in the treatment of late-life depression. In addition, many trials of psychotherapy with older adults exclude those with multi-morbidity. Hence, this trial will confirm whether CBT and PST are efficacious in the treatment of depression in the context of complex medical needs and determine which of these two interventions is most efficacious.

**Trial registration:**

ACTRN12612000854831

## Background

Older age is associated with an increased risk of depression [1]. A systematic review revealed six consistent factors associated with depression in older people. Excepting female gender, physical health and functional impairment were the strongest predictors of late-life depression [2]. Increased rates of depression have been found in older patients with a range of illnesses [3-6]. Indeed, one study demonstrated 83% of those over 75 had more than one health problem, and a psychological and health problem was the second most common co-morbidity [7]. Of even more concern, research confirms that physical illness also increases the risk of suicide amongst depressed older adults [8].

Despite a large number of trials of psychological therapies in young depressed patients [9], there are far fewer studies in older people. The number of trials in the literature has been increasing, which has given rise to numerous reviews of the efficacy of psychotherapeutic interventions for late-life depression [10-14]. Although those reviews varied in which interventions were found to be definitely efficacious, there is some general consensus.

Cognitive Behavioural Therapy (CBT), a therapy based on changing unhelpful beliefs and increasing activity as a treatment for depression, is the most well researched therapy in the treatment of late-life depression [12]. In their Cochrane Review, Wilson and colleagues [12] concluded that CBT was the only definitely efficacious therapy for late-life depression. They used very stringent criteria for trial inclusion, but nonetheless, on this point there is considerable consistency between reviews. That is, CBT is a proven effective treatment for late-life depression [10-14].

In the Cochrane review, Problem Solving Therapy (PST) was considered under the umbrella of CBT [10,12]. However, there are important differences. CBT focuses on restructuring and challenging beliefs that are associated with low mood and behavioural activation, whereas PST focuses on dealing with the problems associated with daily life and shifting negative cognitions into goal directed activity [15]. One review of psychological treatments in older adults [14] that distinguished between PST and CBT, concluded that PST was probably efficacious. However, since that review, there have been a number of additional, well controlled trials that have evaluated PST as a treatment for late-life depression, each of which has supported the efficacy of PST [16-21]. Hence, PST can be regarded as meeting the criteria for a definitely efficacious treatment [22]. Furthermore, in a meta-analysis comparing psychotherapies for adult depression, PST was found to have the lowest drop out rates of any of the therapies, making it a highly acceptable intervention among people suffering from depression [23].

Although there is good evidence to support the efficacy of CBT and PST for the treatment of later life depression, there is a need for further research [13]. Which of these treatments is most efficacious remains unclear. To date, no trials have compared CBT with PST [10]. Research comparing those treatments shown to be most efficacious for the treatment of late life depression is needed in order to ensure that patients are offered the most efficacious intervention. Large trials comparing these treatments can also investigate whether different patients benefit from different treatments. If the different treatments are suited to patients with different characteristics, there may be ways in which interventions can be matched to those patients most likely to benefit from them.

Similarly, there is a pressing need for outcome studies for depressed patients with complex needs. In their meta-analysis, Pinquart and colleagues [10] found that effect sizes were smaller in studies that included people with a co-morbid medical illness. However, there are few trials of the treatment of late-life depression for people with a range of co-morbid physical health problems and patients with multi-morbidity (i.e. two or more concurrent physical and/or psychological disorders are often excluded from the published trials). Only the PROSPECT [24] and IMPACT [18] trials have studied treatment of depression in older medical patients, however, the interventions studied were not exclusively psychological. In these studies, patients were offered a choice of either medication or behavioral treatment. There are, however, some studies in patients with specific illnesses that show that CBT is effective in reducing depressive symptomatology in patients with chronic illnesses often seen in older adults. For example, CBT is successful in reducing depressive symptoms in arthritis and preventing the development of new “cases” of depression over 18 months [25,26]. Similarly, recent research shows that CBT for Chronic Obstructive Pulmonary Disease (COPD) is successful in improving depressive symptoms [27].

Despite these encouraging results, neither study specifically included patients who met criteria for major or minor depression. Indeed, there appear to be no studies of CBT in late life depression where patients were included on the basis of a diagnosis of clinical depression and a comorbid health problem. Two studies investigated the efficacy of CBT for patients scoring above a cut-off score on questionnaires. Both studies (a small trial in stroke survivors [28] and a larger trial in Chronic Obstructive Pulmonary Disease patients [29]) failed to find a benefit of CBT. However, in the stroke study, patients were recruited on the basis of their scores on a screening test (the Beck Depression Inventory), known to be inflated in physically ill populations. Of those allocated to CBT, 69% met criteria for a depressive disorder, in contrast to only 43% of the control group. These initial differences could have masked any treatment effects. There are also problems with the Chronic Obstructive Pulmonary Disease study. Kunik et al. [29] included patients with heightened levels of depression OR anxiety and attempted in an 8 x 1 h program to address both symptoms in groups of 10 patients. The cognitive component (i.e. cognitive restructuring) involved only two sessions, and this may not be sufficient, particularly in older adults, to have conferred benefit [10]. While these studies have some problems, the null findings highlight the importance of trials to confirm that the efficacy of CBT extends to those with comorbid medical problems and late-life depression.

There is more research about the efficacy of PST in the treatment of late life depression in physically ill patients. One early trial in older adults with medical illness found positive results [30], but was uncontrolled. There have since been a number of large trials in the context of particular health conditions. Areán and her colleagues have shown that PST can improve depression in patients with arthritis [31] and in older disabled people with cognitive dysfunction [16,32]. This provides good evidence that at least in some disorders, PST can ameliorate depressive illness even where complicated by the presence of one serious, chronic health problem. Additionally, PST has been found to be effective in disabled older adults (many of whom have chronic illnesses) [33,34] and reduces the risk of post stroke depression [35], as well as reducing depression symptoms in cancer patients [36]. However, the question of whether PST can be applied across the range of health problems common in later life, particularly in those with multi-morbidity, and whether it is as effective as CBT, remains unclear.

### Aims and hypotheses

Although there have been numerous trials of psychological interventions for patients with late-life depression in the past decade, there continue to be major gaps in the literature. Firstly, few studies aim to treat depression in the context of ill health, despite the fact that many older adults have both depression and one or more chronic physical illnesses. There are also few studies that compare different psychotherapies for late-life depression. The PROMISE-D trial aims to bridge these gaps. Specifically, the aim of the study is to evaluate two psychological therapies (PST and CBT), both of which are definitely efficacious for the treatment of late-life depression, for patients with one or more co-morbid physical illness.

We hypothesise that PST and CBT will be superior to a wait-list control group in the treatment of depression for patients with co-morbid health problems. We also aim to determine what baseline characteristics might best predict outcome in each treatment condition. Based on the hypothesised mechanisms of PST, we expect that patients with executive dysfunction (poor score on the Stroop Interference Task [37]) will respond better to PST than CBT [16]. In contrast, we expect patients with excessive rumination (measured by the Ruminative Response Scale; RRS [38]) and patients with affective dysregulation (measured by the Emotion Regulation Questionnaire; ERQ [39]) to respond better to CBT than PST [39,40].

## Methods/design

The procedure of the PROMISE-D trial is illustrated in Figure 1. This study has been designed in accordance with CONSORT criteria [41] and is a randomised controlled trial (RCT) registered with the Australian New Zealand Clinical Trial Registry. Ethical approval has been granted for this study by the University of Sydney Human Research Ethics Committee.

**Figure 1 F1:**
[figure not shown]
Outline of study design.

### Participants

Consecutive adults aged 65 years and older presenting at GP surgeries will be screened for the study. The inclusion criteria are (1) one or more chronic physical illness; (2) a diagnosis of major or minor depressive disorder or dysthymia; (3) if taking anti-depressant medication, a stable dose for > 8 weeks; (4) have not received electroconvulsive therapy (ECT) within 6 months (to exclude memory problems) and (5) sufficient English to complete questionnaires and take part in therapy. Participants will be excluded if they have (1) suicidal intent requiring emergency care; (2) alcohol or drug abuse or dependence; (3) a history of bipolar disorder or cyclothymia; (3) a psychotic illness; (4) cognitive deficits (< 25 on the Telephone Interview for Cognitive Status [TICS] [42]); or (5) have received psychotherapy within the last six months.

Participants will be recruited at their GP surgery when they attend for an appointment. Based on the prevalence of physical health problems amongst older people (60%) (and depressive symptoms high enough to warrant screening amongst those [30%]), and the likely rate of actual disorder from those who screen positive (70%), we anticipate that approximately 1400 older people will need to be screened in order to achieve the 177 participants required for the RCT.

### Procedure

GP surgeries will be sent a letter inviting them to participate in the study. If they agree to be involved, consecutive attendees at participating surgeries who are 65 and over will be asked to complete a one-page double-sided screening questionnaire and post it in a locked box located in the surgery. The screening questionnaire will consist of the Geriatric Depression Scale- Short Form (GDS-SF [43]) and some basic demographic questions (age, gender). Respondents will also be asked to indicate, from a list provided, which chronic illnesses (if any) they have. People who prefer not to complete the questionnaire will be asked to put the unanswered page into the locked box to provide an estimate of how many individuals refused to take part. Participants will be informed that if they give the researchers their details and are eligible for the study, that the researchers will contact them directly.

Those participants who score ≥ 5 on the GDS-SF [43] and have at least one chronic illness will be telephoned by the researchers and asked if they would like to participate in a phone interview. The interview will be used to determine whether they meet the criteria for major or minor depression using the Primary Care Evaluation of Mental Disorders - Depression subscale (PRIME-MD [44]). Their cognitive status will also be assessed via the Telephone Interview for Cognitive Status [42] and more detailed demographic questions will be asked. If they meet criteria for a clinical depression (major or minor) as assessed by the PRIME-MD, the Hamilton Rating Scale for Depression (HAM-D [45]) will also be conducted and participants will be offered the opportunity to take part in the RCT.

Participants who complete the phone interview and are eligible for the RCT will be told about the trial at the end of the phone interview. Those individuals interested in participating will be sent a participant information statement, consent form and the baseline questionnaires (Short Form (36) Health Survey; SF-36 [46]; Geriatric Anxiety Inventory [47]; Ruminative Response Scale [38]; Emotion Regulation Questionnaire [39]). Upon receipt of their consent form and baseline questionnaires, participants will be randomised, by an independent researcher, into one of three conditions: CBT, PST or E-TAU (described below). Medical files will be accessed to get details of current medications (including anti-depressant medication) and to confirm their diagnoses. Participants will then be contacted by a member of the research team and informed of their condition. If allocated to CBT or PST, the researcher will arrange an appointment for their first therapy session, which will be conducted at a local health clinic. During the first session participants in the PST and CBT conditions will complete the Stroop Interference Task [37].

Treatment consists of 10 one hour weekly sessions. All participants will have their depressive symptoms monitored via the administration of the GDS-SF midway through the trial period (i.e. after 5 weeks). If any individual demonstrates a reliable deterioration [48], from trial entry, in GDS-SF score they will be contacted by the research team to determine their ability to continue the trial and to ensure their safety. Post-treatment assessment using PRIME-MD Depression module, GDS-SF and the HAM-D will be conducted. Participants will also be asked to complete the SF-36 to assess their quality of life and the Geriatric Anxiety Inventory to assess co-morbid anxiety symptoms at post-treatment. Follow-up assessments will be conducted six and 12 months after the trial. Data on health care utilisation will be gained from Medicare and the Pharmaceutical Benefits Scheme in order to determine the cost efficacy of the interventions in the two years following treatment.

### Randomisation

Randomisation will be stratified by diagnosis (major depressive episode or minor depression/dysthymia). This will be performed by an independent researcher who has no other involvement in the trial, using computer-generated random numbers.

#### Cognitive behavioural therapy

There are two primary components of CBT: behavioural activation and cognitive restructuring. Behavioural activation teaches patients about the relationship between activity and mood, such that lowering levels of activity results in reductions in mood, creating a vicious cycle often referred to as the lethargy circuit. Participants are encouraged to develop realistic goals that are associated with either mastery (i.e. the feeling of achievement for having completed a goal) or pleasure. Participants are also encouraged to monitor their moods in relation to their goals and other daily activities. Over the course of the therapy, participants are encouraged to gradually increase their involvement in activities. Cognitive restructuring helps patients learn to identify unhelpful thoughts and beliefs in daily situations. Particular strategies are learned to help challenge the validity of their assumptions and to develop more helpful and realistic appraisals in daily situations. Behavioural experiments are developed within session in order to test out unhelpful beliefs. These challenging strategies are applied in daily situations to help participants to gain better control over their thoughts and subsequently their mood.

#### Problem solving therapy

PST teaches patients structured problem solving strategies that they learn to apply to everyday difficulties, as well as to more significant adverse life events, such as divorce or serious medical illness. The program will specifically target those problems arising from their medical conditions. In the first session the patient will receive psychoeducation on depression in general and learn specifically about the mechanics of PST and why it is effective. Therapists will guide patients to generate a list of problems that they are currently experiencing in their lives and select and clearly define a moderately challenging one to focus on. Patients will then identify a goal, related to that problem, that they would like to achieve and brainstorm strategies to meet the goal, producing as many solutions as possible. Following this, patients assess the pros and cons of each solution they have created and choose one or more to implement. They then generate an action plan containing steps by which to carry out this solution. At subsequent sessions the action plan is reviewed and the success (or lack of success) at achieving the goal is discussed, and a new solution is developed if necessary.

#### Enhanced treatment-as-usual

Participants in the E-TAU condition will not receive any specified treatment as a result of the trial. However, they will be free to pursue treatment as usual during the course of the 10 week trial period. Any treatments initiated during the 10 week treatment phase of the trial will be carefully monitored. However, GPs will receive no information about the participant’s mood during the 10 week treatment phase of the trial. Because it would unethical to have assessed a person with a depressive disorder and provide no treatment for such a lengthy period of time, once post-treatment assessments are completed, GPs of participants who still meet criteria for a depressive disorder will be informed of the participant’s depression status.

### Outcome measures

The primary outcome will be diagnoses of depression according to the PRIME-MD Depression module. In order to allow for multi-modal assessment we will also measure participants’ depression using the GDS-SF [43] and clinician-rated severity according to the HAM-D [45]. Two secondary outcomes will be measured. Quality of life will be assessed with the SF-36 [46] and anxiety will be measured using the Geriatric Anxiety Inventory [47]. These assessments will be conducted by a researcher who remains blind to the participant’s treatment allocation. Blindness will be confirmed by having the independent researcher guess the group that they think each participant belongs to at the end of the treatment period.

As we are interested in which factors affect treatment success, we will also be taking a number of process measures. Executive function will measured using the Stroop Interference Task [37]. For logistical reasons only participants in PST and CBT conditions will be administered the Stroop task because it requires face-to-face administration. The Stroop will be used as a predictor of treatment outcome and not an outcome measures. All participants will be assessed for level of rumination (via the Ruminative Response Scale [38]) and affective regulation (via the Emotion Regulation Questionnaire [39]).

Additionally, demographic variables such as ethnicity and level of education will be recorded, as well as more specific information about previous depressive diagnoses and treatment. In order to confirm details of their chronic illness(es), RCT participants will also be asked to consent to the research team accessing their medical files.

### Analysis

#### Sample size

177 participants will be recruited to the RCT. In order to achieve 95% power and α = 0.05, 47 participants per group are needed. Allowing for 20% attrition, this requires 59 participants per group.

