##### Sample size

The primary outcomes are a diagnosis of depression according to PRIME-MD and severity of depression according to the HDS and GDS. In a recent meta-analysis, the average effect size for CBT (including PST trials) was 1.06 and for PST was 1.00 [10]. To be conservative, we have used the smaller ES of 1.00. According to G-power, we would need only 25 participants per group have 95% power to detect a significant difference (p < 0.05) between the 2 active treatments and the control condition [53]. However, we are also interested in the relative efficacy of each of the 2 interventions. Given that these two treatments have never been compared in any clinical setting, we determined that to be conservative, we should power the study to identify even small differences in effect sizes (Cohen’s D = 0.25) between the two treatments. In order to be able to observe a difference between the two groups of 0.25 with 80% power and a significance level of 0.05, we need 59 participants per group. That is, 177 participants in total.

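### The two sample-size paragraphs justify 59 per group on incompatible grounds, and 59 gives about 27% power, not 80%, for the stated CBT–PST difference of 0.25

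*Protocol article*

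**What the plan says.** The article has two Sample size paragraphs.

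- **Directly under Analysis.** For 95% power at α = 0.05, it says "47 participants per group are needed. Allowing for 20% attrition, this requires 59 participants per group". No comparison, effect size or sidedness is given. Here 59 is the recruited number and 47 the number needed.
- **Under Statistical analysis.** The comparison of each therapy with control is taken at an effect size of 1.00 and is said to need 25 per group for 95% power. The paragraph then turns to CBT against PST, sets the difference to be detected at Cohen's d = 0.25 with 80% power and a 0.05 significance level, and concludes: "we need 59 participants per group. That is, 177 participants in total". Attrition is not mentioned.

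On the choice of 1.00, the second paragraph says "To be conservative, we have used the smaller ES of 1.00"; the alternative was 1.06, from the same meta-analysis. The Background says that this meta-analysis "found that effect sizes were smaller in studies that included people with a co-morbid medical illness". Under Participants, at least one chronic physical illness is an inclusion criterion.

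**The concern.** One recruitment target has two derivations. They differ in the power claimed (95% against 80%) and in whether 59 already contains the attrition allowance. One names the comparison and the effect size; the other names neither. A reader cannot tell what the trial is powered to detect.

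The stake is greatest for CBT against PST. Finding out which therapy is more efficacious is a declared aim (Abstract, Discussion; Conclusion), and the article says that the study is powered for even a small difference. If that power does not exist, a non-significant CBT–PST result could be misread as showing that the therapies work equally well.

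The word conservative raises a smaller doubt. An average over all trials is not cautious for a population in which its own source found smaller effects.

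**Working it through.** **Inputs from the article:** 47 and 59 per group, 20% attrition, 95% and 80% power, α = 0.05, d = 1.00 (therapy against control), d = 0.25 (CBT against PST). **Assumed:** two-sided test, two independent groups, one time point, no baseline adjustment, no clustering. The article gives no sidedness, correlation or intraclass correlation.

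**1. Attrition step.** 47/(1 − 0.20) = 58.75, so 59. This reproduces. In reverse, 59 × 0.80 = 47.2.

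**2. The 25 per group.** n = 2(z₀.₉₇₅ + z_power)²/d². At d = 1.00 and 95% power: 2(1.960 + 1.645)²/1 = 26.0. The noncentral t gives 27. The stated 25 is within two patients of this.

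**3. The 47 per group at 95% power.**
- d = 1.00 needs 27 (step 2).
- d = 0.25 needs 26.0/0.0625 = 416 (noncentral t: 417).
- Solving for d: √(26.0/47) = 0.74 (noncentral t: 0.75).

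So 47 matches neither stated effect size. It matches d of about 0.75, which appears nowhere.

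**4. The 59 per group at 80% power for d = 0.25.**
- Required: 2(1.960 + 0.842)²/0.25² = 15.7/0.0625 = 251.2, so 252 (noncentral t: 253). One-sided: 198 to 199.
- Power with 59: noncentrality 0.25 × √(59/2) = 1.358; Φ(1.358 − 1.960) = 27%.
- Power with 47: noncentrality 0.25 × √(47/2) = 1.212; Φ(1.212 − 1.960) = 23% (noncentral t: 22%).

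**5. Attrition across the two paragraphs.** If 59 are needed and 20% are lost, recruitment would be 59/0.80 = 73.75, so 74 per group. If 59 are recruited, about 47 remain.

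**6. What the design can detect (noncentral t).**

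| Assessed per arm | d at 80% power | d at 95% power |
|---|---|---|
| 59 | 0.52 | 0.67 |
| 47 | 0.58 | 0.75 |

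**7. Therapy against control with 47 per arm.** The article gives no effect size for medically ill patients, so the range is assumed.

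| d | 1.00 | 0.80 | 0.75 | 0.60 | 0.50 | 0.40 |
|---|---|---|---|---|---|---|
| Power | 99.8% | 97% | 95% | 82% | 67% | 48% |

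**The case against.** **Different powers for one N are not in themselves a contradiction.** The same 59 can give 95% power for one contrast and 80% for another. That would answer the point if the paragraph under Analysis named its contrast, but it does not. The two uses of 59, with and without attrition, still conflict. A reader might also count the 25 as a third rival justification for 59, or take 59 in the second paragraph as the number analysed. The text supports neither: 25 is offered only for the control comparison, and the paragraph says what is needed without saying whether that means recruited or assessed.

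**The planned analysis is more efficient than a t-test.** Linear mixed models with a baseline covariate are specified, so it would be too strong to say that 47 gives 95% power only for d of 0.75 or more. With one follow-up, adjustment multiplies the detectable d by √(1 − ρ²). At ρ = 0.5 that is 0.75 × 0.866 = 0.65, and over ρ from 0.3 to 0.7 it runs from 0.72 to 0.54. This stands as a qualification, but it does not rescue d = 0.25. At ρ = 0.5 the requirement is 252 × 0.75 = 189 per group. Averaging three follow-ups multiplies n by (1 + 2ρ)/3 − ρ², giving 105 per group at ρ = 0.5. It gives 57 at ρ = 0.8, and even there 47 assessed yields 72% power. No such correlation is stated, and clustering by primary care service would work the other way.

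**The 0.25 may have been another effect size.** Read as Cohen's f, 0.25 needs 53 per group in a three-group ANOVA or 64 in two groups. Neither is 59, and the article names Cohen's d.

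**The 1.00 does not set N.** This stands. It yields only the 25 per group. A reader might infer that the therapy-against-control comparison is underpowered, but the document does not show that. With 47 per arm, power stays at about 80% or more down to d of about 0.58, so the effect would have to shrink by more than about 40%. The 67% at d = 0.50 would follow from a halving of the effect, and the article gives no size for the reduction.

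**Conclusion.** The concern holds. The two paragraphs give incompatible bases for 59 per group, and neither follows from its stated inputs. The attrition arithmetic is right, but the 47 it starts from has no stated effect size and corresponds to d of about 0.75. The serious numerical fault is the claim of 80% power for d = 0.25: by an unadjusted two-sided 5% t-test, power is about 27% with 59 per group and about 22% with 47, and about 253 assessed per group would be needed. Baseline adjustment and repeated measures would raise these powers and clustering would lower them, by amounts the article gives no means to calculate.

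Calling 1.00 conservative is inconsistent with the Background. That is a fault of justification and not evidence that the control comparison lacks power.

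**What to change.** Keep N at 177 and replace both paragraphs with one statement:

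- 59 randomised and about 47 assessed per arm, allowing for 20% attrition.
- Any pairwise contrast has 80% power for d of about 0.58 and 95% power for d of about 0.75, two-sided 5%, before baseline adjustment and clustering, for which no correlation or intraclass correlation is given.
- The claim of 80% power for d = 0.25 is withdrawn. The CBT–PST comparison has only about 22% power for that difference on this basis, so a null result cannot be read as equivalence.
- The word conservative is removed for 1.00, or a note is added that the effect may be smaller in medically ill patients.

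The sponsor should confirm the sidedness. The change leaves recruitment and the analysis method as they are. The cost is that the stated power becomes less favourable, most visibly for the comparison of the two therapies. Resizing to keep the 0.25 claim would, on the unadjusted basis, take 253/0.80 = 316.25, so 317 per group, against 59 now.
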